|                                                  |                                                                                                                                                                                                                                                                                                                                                                                                                                                                                                                                                                                                                                                                                                                                                                                                |
|--------------------------------------------------|------------------------------------------------------------------------------------------------------------------------------------------------------------------------------------------------------------------------------------------------------------------------------------------------------------------------------------------------------------------------------------------------------------------------------------------------------------------------------------------------------------------------------------------------------------------------------------------------------------------------------------------------------------------------------------------------------------------------------------------------------------------------------------------------|
| 
Expected total number of patients:
 | 
d) Patient is immunocompromised;
e) Patient is on a course of anti-inflammatories or antibiotics;
f) Patient has diabetes mellitus (DM).
 
60 patients, 30 in the treatment group and 30 in the control group, stratified as follows:
 
Arm 1) Considered the control group, this arm will receive conventional treatment from the date of admission to the hospital and will also receive the protocol with the laser turned off, therefore without any effect.
 
Arm 2) This arm will receive the laser treatment within 30 minutes after the infusion of antivenom serum at a dose of 4j/cm^2.
                                                                                                                                                      |

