| 
EVALUATION SCHEME
          | 
Patients will be evaluated with the same parameters irrespective of the group to which they were allocated at the time of admission, and at 24 and 48 hours in relation to clinical and laboratory aspects.
                                                                                                                                                                                                                                                                                                                                                                                                                                                                                                                                                                                                                                                                                                                                                                                                                 |
| 
STATISTICAL CONSIDERATIONS
 | 
Number of patients:
 
A priori, 60 patients in order to evaluate the effectiveness and safety of low-intensity laser in sites of snakebites involving the genus Bothrops.
 
Statistical generalities:
 
This study foresees the performance of an interim analysis when the groups reach half of their recruitment, i.e., 15 patients in each group. This analysis will be able to identify variations related to the primary outcome and will indicate the need for continuity, restructuring, or finalization of the study. Quantitative variables will be calculated for frequency and proportions, with the calculation of means.
 
Feasibility outcomes were analyzed using descriptive statistics as proportions. Trial outcomes were reported as means and standard deviations. We report the outcomes using means and standard deviations, and we conducted inferential analysis on our data in order to report the differences between the two groups. Mean values
 |

[figure not shown][figure not shown]

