In these areas, among the medically important snakes involved in the envenomations, *Bothrops jararacussu*, popularly known as « jararacuçu », is found in Brazil, Bolivia, Paraguay and northeastern Argentina. In Brazil, it is also the snake with the highest venom production and injection capacity (400 mg)(10), and one of the most important venomous vipers of the viperidae family in Latin America, reaching a maximum length of 220 cm(11).

The venom of species belonging to the genus *Bothrops* has a predominantly proteolytic, coagulant, hemorrhagic, inflammatory, edematogenic and myotoxic effect(12). The clinical signs exhibited by *Bothrops* envenomations are due to the various components that are isolated from these secretions, such as the hemorrhagic factor, i.e., proteases that act in blood coagulation causing coagulation disorders, proteolytic enzymes and myotoxins(13). Among the main enzymatic proteins with myotoxic activity found in snake venoms are proteolytic enzymes and phospholipases(12)(14).

*Bothrops* venom can cause systemic effects, such as bleeding in pre-existing wounds, cardiovascular and renal alterations, gingival bleeding, epistaxis, hematemesis, hematuria, uterine bleeding (pregnant women), vomiting, nausea, sweating, arterial hypotension and shock(15). In envenomations by these species, the

victim will commonly have evident local effects, which may vary in intensity, and which are represented by pain and edema that sets in early and evolves progressively. Ecchymosis, bleeding, ganglionic enlargement, blisters and necrosis may also appear, and it is possible to have functional or even anatomical loss of the affected limb as sequelae(16).

Among the local reactions, cell necrosis can result in loss of tissue function in the affected limb(17). Thus, the myonecrosis caused by *Bothrops* venoms may have an indirect action as a result of the degradation of blood, vessels and ischemia caused by metalloproteinase or by the direct effect of the homologous myotoxic phospholipases A2 (PLA2s) on the plasmatic membrane of skeletal muscle cells(18).

Metalloproteinases, on the other hand, have a hemorrhagic action in *Bothrops* venoms, causing hemorrhage followed by myonecrosis and arterial necrosis, and enhance myotoxicity as a result of reduced muscle perfusion and circulatory deprivation, which also affects muscle regeneration(19).

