An increase in the regional lymph nodes that drain the site of the bite and bruises can also be observed a few hours after envenomation, especially if there is a delay in hospital care for the patient(20). In the first 24 hours, blisters and tissue necrosis may be evident. In addition, the snakebite may present or develop complications such as bacterial infections(18), with cellulitis and/or abscess, especially in people classified as having moderate or severe injuries(6).

Thus, the inflammation triggered by envenomation plays a fundamental role in local injury, and is characterized by increased vascular permeability, formation of edema and infiltration of polymorphonuclear leukocytes and macrophages(21). However, skeletal muscle regeneration depends on the proliferation and differentiation of satellite cells, which are normally quiescent but, in response to

stimuli such as muscle trauma, become activated, proliferate and fuse with the affected fibers or with new myofibers(21).

The neutralization of this process and the clearance of the venom depends on several factors, including the potency of the antivenom, the length of time between the bite occurring and the administration of serum therapy as well as the route of administration(22). Some factors that can potentiate the local effects venom and, consequently, the appearance of complications such as the adoption of non-recommended measures, i.e., the use of constriction bands, tourniquets, incision, aspiration, and ice therapy are contraindicated(22). However, the antivenom has an immediate action on the circulating venom, but often fails to have the desired and satisfactory action at the site of the bite(23).

Several studies have invested in the search for appropriate procedures to promote muscle regeneration in cases of *Bothrops* envenomations, since antivenom has a predominantly systemic rather than local action(24). Although much progress has been made in treating the systemic effects of snake venoms, treatments for local damage are directed towards hygiene only, with a recommendation for cleaning with saline or soap and water, with cleaning as the only protocol for local care(25)(24). Within this therapeutic concept at the injury site, laboratory research in mice in controlled environments has examined the use of laser therapy as an option for tissue regeneration(25).

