### 7.2. Inclusion criteria

Patients eligible for the study must meet the following characteristics:

- a) Less than 24 hours have passed since the bite;
- b) Must be over 18 years of age;
- c) Not having performed serum therapy for the current *Bothrops* snakebite at another institution.

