### 13.2 Statistical and analytical plans

Feasibility outcomes were analyzed using descriptive statistics as proportions. Trial outcomes were reported as means and standard deviations. We report the outcomes using means and standard deviations, and we conducted inferential analysis on our data in order to report the differences between the two groups. Mean values of creatine phosphokinase activity, pain intensity, circumference measurement ratio, extent of edema, difference between the bite-site temperature and that of the contralateral limb, and disability assessments, were compared using the t-test for independent samples, at 48 hours after admission. A Kaplan-Meier survival analysis with a log-rank test was performed to detect differences in the time elapsed from admission to the day of reduction by 50% in creatine phosphokinase activity, pain intensity, circumference measurement ratio, extent of edema and difference between the bite-site temperature and that of the contralateral limb between the intervention and comparator groups, at two points - on 24 and on 48 hours after admission. The comparison of the frequency of use of analgesics, secondary infections and necrosis in a follow-up of 48 hours, between the intervention and comparator groups, was made using the Chi-square or Fisher's exact test; odds ratios with 95% confidence intervals were obtained. The Kruskal-Wallis rank sum test was used to compare the disability scores between groups, for each domain score and for the summary score. Statistical analyses were performed in the R software in the IDE Rstudio environment (version 4.1.2), and the significance level of the tests was 0.05.

[figure not shown][figure not shown]

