2.1 Origin: • 1-Manaus 2-Municipality Where? \_\_\_\_\_  
2.2 Date of the accident: \_\_\_\_/\_\_\_\_/\_\_\_\_  
2.3 Estimate time of the accident: \_\_\_\_:\_\_\_\_  
2.4 Date of admission to FMT-HVD: \_\_\_\_/\_\_\_\_/\_\_\_\_ 2.5 Time of Admission: \_\_\_\_:\_\_\_\_  

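### The 48-hour t-tests and the log-rank test leave out the 0 to 24 h delay from bite to admission, a recorded variable that could add precision at almost no cost

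*Protocol*

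**What the plan says.** - **Delay matters.** Section 4.1 lists among the determinants of venom neutralisation and clearance "the length of time between the bite occurring and the administration of serum therapy". It describes the local effects as "pain and edema that sets in early and evolves progressively".
- **Entry window.** The first inclusion criterion in section 7.2 is "Less than 24 hours have passed since the bite".
- **Analysis.** Section 13.2 and the synopsis state that the means of six outcomes (CK, pain, circumference ratio, edema extent, temperature difference, disability) "were compared using the t-test for independent samples, at 48 hours after admission". For the first five, the time from admission to a 50% reduction is compared by Kaplan-Meier and log-rank test. No covariate or stratum is named, and "the significance level of the tests was 0.05".
- **Allocation.** Sections 8.2 and 12.1.1 describe randomisation to two groups without a balancing factor. The synopsis has "60 patients, 30 in the treatment group and 30 in the control group, stratified as follows", but only the two arms follow.
- **Data held.** Attachment A records the accident date (2.2), "2.3 Estimate time of the accident", and the date and time of admission (2.4, 2.5). No planned analysis uses them.
- **Sample size.** The synopsis gives "60 patients in order to evaluate the effectiveness and safety of low-intensity laser", with no effect size, standard deviation or power behind the number.

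**The concern.** Entry from 0 to under 24 h after the bite puts an assessment at 48 h after admission anywhere from 48 h to nearly 72 h after the bite. By the protocol's own account the lesion is still changing during the entry window, so part of the spread in each 48-h outcome may reflect arrival time and not treatment. An unadjusted test leaves that spread in the error term.

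The time-to-50%-reduction endpoint has a further weakness. Its reference is presumably the admission value, since time runs from admission. An early arrival may be measured before the peak and a late arrival at or past it. Whether the event can occur within 48 h would then depend partly on when the patient came in.

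At stake is the power of a small trial whose sample size has no stated derivation, and so no documented margin.

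**Working it through.** **Inputs from the protocol:** 30 per arm; alpha 0.05 (taken as two-sided; sidedness is not stated); entry 0 to under 24 h. **Not in the protocol, so assumed:** the distribution of delay, the share of late presenters, the correlation r of delay with a 48-h outcome, and the time course of the lesion. The planned size of 60 cannot be reproduced because no inputs are stated.

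**1. What 30 per arm can detect.** The standard error of a mean difference, in outcome SDs, is sqrt(2/30) = 0.258. At 80% power the detectable difference is (1.960 + 0.842) × 0.258 = 0.72 SD by the normal approximation, or 0.74 SD by the t distribution.

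**2. Precision lost by omitting delay.** Adjustment multiplies residual variance by 1 − r², so omission inflates it by 1/(1 − r²). For r = 0.3 this is 1/0.91 = 1.10; for r = 0.4 it is 1/0.84 = 1.19. The table starts from 80% unadjusted power. The last two columns take an imbalance in mean delay at its 95% limit, where the shift is r × 1.96 × 0.258.

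| r (assumed) | Variance inflation | Power if adjusted | Unadjusted n per arm to match | Shift (SD) | Type I error given that imbalance |
|---|---|---|---|---|---|
| 0.2 | 1.04 | 81.6% | 32 | 0.10 | 6.3% |
| 0.3 | 1.10 | 83.6% | 33 | 0.15 | 7.9% |
| 0.4 | 1.19 | 86.4% | 36 | 0.20 | 10.1% |
| 0.5 | 1.33 | 89.9% | 40 | 0.25 | 12.9% |
| 0.6 | 1.56 | 93.8% | 47 | 0.30 | 16.4% |

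These are marginal correlations. If the admission value is in the model, the relevant r is the partial correlation given that value. It will be smaller to the extent that the admission value already carries the delay effect.

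**3. Size of chance imbalance.** The SD of the difference in mean delay is SD × sqrt(2/30). If delay is uniform over 0 to 24 h, its SD is 24/sqrt(12) = 6.93 h, the SD of the difference is 1.79 h and the 95% range is ±3.5 h. With an SD of 5 h the range is ±2.5 h; with 3 h it is ±1.5 h.

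The same point in counts uses two independent binomials of size 30. The chance that the arms differ by 6 or more late presenters (20 percentage points) is 15.5% if half are late and 12.0% if 30% are. With half late, a gap of 8 or more has a chance of 5.2%.

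**4. What a 20-point imbalance does.** With half late, late and early patients differ by r/0.5 = 0.6 to 0.8 SD for r = 0.3 to 0.4. The arm difference moves by 0.20 × 0.6 = 0.12 to 0.20 × 0.8 = 0.16 SD. Against a standard error of 0.258 that is 0.46 to 0.62, or about half a standard error.

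**5. The 50%-reduction endpoint, by illustration.** Assume a marker that rises linearly to a peak and then halves at a fixed rate. The ratio of the 48-h value to the admission value must be 0.5 or less for the event to have occurred.

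- Peak 24 h, half-life 24 h: 3.7 for arrival at 3 h, 1.7 at 6 h, 0.71 at 12 h, 0.40 at 18 h, 0.27 at 23 h. Only late arrivals reach the event.
- Peak 6 h, half-life 24 h: 1.73 at 1 h, 0.55 at 3 h, 0.25 from 6 h on.
- Peak 6 h, half-life 12 h: 0.50 at 1 h and lower after. Everyone reaches it.
- Peak 36 h, half-life 36 h: still 0.80 at 23 h. No one reaches it.

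The endpoint depends on arrival time under the first two courses. Under the last two, reaching the event by 48 h does not.

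**The case against.** **Randomisation already deals with delay.** This stands. Delay is balanced in expectation, the unadjusted test keeps its 5% type I error over repeated trials, and ordinary chance imbalance is already in the standard error. A reader might infer that nothing balances delay, or that the treatment comparison is biased by it. The protocol does not support that: patients are randomised on D1. The raised error rates in the table apply only given an unlucky imbalance.

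**Not every outcome is timed from admission.** Also correct. The D2 and D3 visits run from the first laser application, and the 48-h follow-up for infection, necrosis and analgesic use names no origin. The admission clock is explicit for the t-tests and the log-rank analysis, and the point is confined to those. That the two clocks differ is a separate matter to reconcile.

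**The protocol also calls antivenom action mainly systemic.** Section 4.1 says that it often falls short at the bite, while most analysed outcomes are local. This weakens the route through late antivenom. It leaves the other route, progression of the local lesion after the bite.

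**Adjusting for the admission value may be enough.** It would probably absorb part of the effect, so 10% to 19% is towards the upper end if that value is in the model. A reader might infer that baseline adjustment cannot help; nothing in the protocol shows this.

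**Covariates belong in the statistical analysis plan.** That plan is not at hand and may name some. Section 13.2, however, does not defer: it names unadjusted tests for these outcomes.

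**Conclusion.** The point holds as one of efficiency, not validity. The protocol names delay as influential, records the times needed to compute it, and then specifies analyses that ignore it. For r = 0.3 to 0.4 the loss is a 10% to 19% inflation of residual variance, equivalent to needing about 33 to 36 patients per arm unadjusted in place of 30. A 20-point imbalance in late presenters would move the result by about half a standard error. All these sizes rest on an assumed correlation and late share, and are smaller if the admission value is also in the model.

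The time-to-50%-reduction endpoint is the most exposed, but how far cannot be fixed without a time course. It would go too far to say that the planned design would produce a false laser effect, or that allocation must be stratified by delay. The first confuses sampling error with bias. The second is a trade-off in a single-centre trial of 60, and the protocol gives no basis for any particular cut-off.

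**What to change.** In section 13.2, and in the matching synopsis text:

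1. Replace the t-tests for the 48-h continuous outcomes with a linear model (ANCOVA) containing arm, the admission value where it was measured, and time from bite to admission, computed from items 2.2 to 2.5 of Attachment A. Use bite-to-admission time because the form as shown carries no time of antivenom.
2. Adjust the time-to-50%-reduction analysis for the same delay, by a Cox model or a delay-stratified log-rank test, and state that the reference is the admission value if that is intended.

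Stratifying the allocation by delay is optional, and falls away if the list is already fixed.

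The cost is one degree of freedom for delay and no new data. Bite time is a patient estimate, so the measured delay is imprecise and the gain somewhat smaller than with an exact time.

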#### **a. 4.2 Study Center**

The Fundação de Medicina Tropical Heitor Vieira Dourado (FMT-HVD) is located in the city of Manaus, Amazonas, and is considered a national and world reference center for the treatment of tropical diseases, especially for events related to venomous animals. currently, it represents the reference center for infectious, parasitic, and dermatological diseases in the state of Amazonas, with 40 medical offices and more than 250,000 health consultations/year; 150 beds, 10 of which are in the intensive care unit; 14 beds dedicated to clinical research; an electronic medical record for medical information with Idoctor® system, allowing faster monitoring in clinical trials; a clinical analysis laboratory and staff trained in good clinical practices).

In addition, since 2005, the foundation has been part of the National Network of Clinical Research in Teaching Hospitals (NNCR), which is an initiative of the Ministry of Health (MH) and the Ministry of Science and Technology (MST) that seeks to promote best research practices geared towards the needs of the public health network.

The network prioritizes the development of clinical trials of drugs, procedures, equipment, and diagnostic devices, of interest to the SUS. The objective of these 19 centers is that the regional training resulting from targeted national integration promotes the acceleration of the growth and scientific capacity of each of these centers. In this way, the centers will be able to develop their own tools capable of solving country-specific challenges.

In this sense, individuals treated in the hospital network in the state of Amazonas are referred to the service in question for the treatment and follow-up

[figure not shown][figure not shown]

of those involved in snakebites, as this unit is a reference for this type of health problem in the state. In Manaus, FMT-HVD is the only hospital unit that dispenses snakebite antivenom.

The snakebite victims hospitalized at FMT-HVD in the period from 1974 to 1984 registered a total of 514 victims. From 1974 to 2012, with an increase in the incidence of snakebites in the 1990s, which peaked in 1998, with 554 cases at FMT-HVD, since the beginning, the epidemiological surveillance of snakebites in the state of Amazonas has shown that rural activities are closely associated with the occurrence of this problem. In the 1990s, the development of sustainable forestry, fishing, and agriculture in the state was stimulated as a result of official government support for the creation of the free green zone program.

Thus, FMT-HVD represents an important site for the development of this clinical study in the face of a sufficient number of attendances for the recruitment of victims of *Bothrops* envenomations.

[figure not shown][figure not shown]

---

## 5. STUDY OBJECTIVES

### 5.1 Primary

To evaluate the effectiveness of low-power laser in the recovery of acute local manifestations in victims of *Bothrops* envenomations.

Clinical and biological tolerability:

- Clinical tolerability: No appearance of myonecrosis.
- Biological safety: CK (creatine kinase).

